### Data monitoring

A group of independent experts with different competences will form a DSMB in order to monitor patient safety and treatment efficacy data while the randomized control trial is ongoing. The board will periodically, at its discretion, review the trial outcome data by the study group plus any other information required and make recommendations to the steering committee. None of the board members is involved in the study implementation or funding of the study. The steering committee is composed of trial investigators as per the title page and two independent members, and chaired by the Head of Department Obstetrics and Gynaecology, Makerere University, Kampala.

Since safety is one of the main issues under study, an interim analysis for safety profile will be done by an independent statistician blinded for treatment allocation when 50% of the data have been collected and entry done. The results will be shared with the DSMB, who will then have a discussion with the steering committee who decide on the continuation of the trial. Annual progress reports are submitted to the Institutional Review Board (IRB) and Uganda National Council for Science and Technology (UNCST) ethical bodies and protocol amendments made if indicated. The trial will not be stopped in case of futility, unless the DSMB advises otherwise and approved by the steering committee. The funders will not have access to the trial data to avoid bias from competing interests.

### Harms

Categories of serious adverse events (SAEs) in this study include death, disability/incapacity, life-threatening sepsis, hospitalization longer than 48 h and blood transfusion for severe hemorrhage. A SAE will be considered unexpected if it is not described in the protocol. SAEs will be recorded as study related only if the participant has signed the consent form and started the intervention. These events will be recorded throughout the time the participant is admitted to the health facility. SAEs occurring after the participant has completed the first follow-up visit will not be reported unless the principal investigator feels that the event may have been caused by the protocol procedure. The PI will promptly inform the institutional review board if a SAE occurs. In the case of physical injury resulting from participation in the study, participants will receive medical treatment at a public health facility until resolution or stabilization.

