In the case that no complete abortion has been achieved within 24 h from the time the first dose of misoprostol was administered, a doctor performs a surgical method of uterine evacuation using MVA or blunt curettage. Patients can also be discontinued from medical management and surgical management instituted if their condition worsens during treatment or on request. All participants are discharged 4 h after completing the abortion if there are no complications. Before discharge, women receive detailed information regarding abnormal symptoms (fever, foul smelling vaginal discharge, bleeding and pain), when to seek care, and contraceptive counselling and provision, and advised to return for a follow-up visit 14 days after treatment. A detailed description of the study participant timeline is provided in Fig. 2.

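### The Harms section ends SAE capture at two different points, so serious events between discharge and the day-14 visit may go unrecorded

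*Protocol article*

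**What the plan says.** The Harms section of the protocol article lists the SAE categories as "death, disability/incapacity, life-threatening sepsis, hospitalization longer than 48 h and blood transfusion for severe hemorrhage". Three rules on capture follow.

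- **Label:** "SAEs will be recorded as study related only if the participant has signed the consent form and started the intervention".
- **Recording:** "These events will be recorded throughout the time the participant is admitted to the health facility".
- **Cut-off:** "SAEs occurring after the participant has completed the first follow-up visit will not be reported unless the principal investigator feels" that the protocol procedure may have caused the event.

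The Procedure section sets the timing. Surgical evacuation follows "In the case that no complete abortion has been achieved within 24 h from the time the first dose of misoprostol was administered". On leaving the facility it says "All participants are discharged 4 h after completing the abortion if there are no complications". The follow-up visit is 14 days after treatment.

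The Outcomes section collects several harms at the two-week visit in both arms: excessive bleeding, pain, sepsis, unscheduled visits to the study site, additional medical treatment and side effects. Data monitoring introduces the interim safety analysis, at 50% of the data, with the words "Since safety is one of the main issues under study".

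**The concern.** The recording rule and the cut-off rule stand next to each other and point to different ends of the SAE window. The first ties recording to the admission. The second makes sense only if SAEs are reported up to the first follow-up visit. Most women will have gone home long before that visit, so the rule a site follows decides whether a post-discharge SAE is captured.

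This matters because safety is in the trial's title and aim, and because the interim safety results inform the decision on continuing. The protocol itself expects possible trouble after discharge: women are told which abnormal symptoms should bring them back. With eight facilities, both readings could be applied in good faith, and SAE counts would then not mean the same thing at every site.

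A second, smaller point concerns the start. The study-related label depends on the intervention having begun, but that moment is not defined. What is randomised is assessment and treatment by a type of provider, so the start could be the clinical assessment or the first dose.

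**Working it through.** The plan states no figure on this point, so the check is a comparison of texts plus simple arithmetic for the disputed interval.

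**1. Length of the disputed interval.** Inputs from the Procedure section: completion by 24 h after the first dose at the latest (otherwise surgery), discharge 4 h after an uncomplicated completion, and a visit at 14 days.

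- Latest discharge after an uncomplicated medical completion: 24 + 4 = 28 h after the first dose.
- Visit, if the 14 days run from the first dose: 14 × 24 = 336 h.
- Interval between the two: 336 − 28 = 308 h, and 308/336 = 92%.
- If the 14 days run from a completion at 24 h, the visit falls at 24 + 336 = 360 h and the interval is 360 − 28 = 332 h, again 92% (332/360).

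Under the admission reading, 308 to 332 h lie outside SAE recording for such a woman. Under the follow-up-visit reading, 0 h do. Women with complications or surgery may stay longer, and their interval is then shorter.

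**2. What the two-week outcomes already cover.** Each SAE category in Harms is set against Outcomes:

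| SAE category | Named as a two-week outcome? |
|---|---|
| Death | No |
| Disability or incapacity | No |
| Life-threatening sepsis | Yes, under a broader definition of sepsis |
| Hospital stay over 48 h | No; a return to the study site would count as an unscheduled visit |
| Transfusion for severe haemorrhage | No; excessive bleeding and additional treatment are collected |

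Unscheduled visits count only presentations at the study site, so an admission elsewhere is not one. The outcomes also depend on a visit that women are advised to attend. A woman who has died or is in hospital cannot attend. The sample size allows 5% loss to follow-up, which is 1192 − 1132 = 60 women; the article does not say at what stage they would be lost.

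**3. The start of the window.** The label rule says when an SAE counts as study related. It does not say that earlier events go unrecorded. The following sentence opens by referring back to these events, which could mean all SAEs or only the labelled ones. The text does not settle this.

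**The case against.** The case against is substantial, and much of it stands.

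- The admission sentence does not say that recording happens only then. It can be read as continuous recording at the bedside, with reporting running on to the visit. A reader might infer that discharge to day 14 is definitely excluded. The documents do not support that: it is one of two readings, and the cut-off sentence points the other way.
- A woman readmitted to the study facility is again an inpatient there, so even the narrow rule can cover her. The clearest exposure is events at home or at other facilities.
- A reader might infer that late bleeding and infection are missed. They are not: both are two-week outcomes in both arms. At least two phone contacts are held for each woman and reasons for loss are sought, so a death could surface that way. The monitoring board may also ask for further information.
- A reader might infer from the label rule that events between randomisation and first dose are dropped and that the intention-to-treat comparison is broken. The rule attaches a label, does not equate the start with the first dose, and removes nobody from the analysis.
- The 92% is a share of time. A reader might take it as the share of risk missed, but the article gives neither a rate nor a timing of SAEs.
- The window is the same in both arms. Staffing is unequal (37 physicians against 138 midwives and other nurse-midwifery staff), so waiting times might differ, but the article reports none and shows no difference in capture by arm.

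It can also be said that this is a condensed article and that SAE detail belongs in the full protocol. That would answer an omission. It does not answer two adjacent printed rules with different end points.

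**Conclusion.** The point holds as an inconsistency in the stated end of SAE capture. For a woman with an uncomplicated completion by 24 h, the two rules differ by roughly 308 h or more out of about two weeks. If a site follows the admission sentence, a post-discharge death, disability, transfusion or stay over 48 h may not be recorded as an SAE, above all when it happens away from the study facility. These are the most serious categories, and the two-week outcomes do not name them. The number of events at stake cannot be computed from the documents, and no bias between arms is shown. The undefined start of the intervention is a lesser ambiguity in the same paragraph. The correction is worth making because safety is a main question of the trial and the remedy is cheap.

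**What to change.** Reconcile the Harms sentences into one window. Record all SAEs in every randomised woman from randomisation to the day-14 visit, including events at other facilities learned of at that visit or by phone. Report them by allocated arm whether or not treatment had begun, and judge relatedness separately from recording. Keep the principal investigator's judgement rule only for events after that visit.

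Recruitment began on 14 August 2018, before the article appeared, so the clarification should also state which reading sites have used so far and, if it was the narrower one, whether earlier participants' day-14 records can be checked for the unnamed categories.

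The cost is a wording change in the protocol and case record form, a note to the sites and a few more SAE forms. The visit and the phone contacts already exist.

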### Confidentiality

Data tools and instruments are stored securely and access restricted to authorized study team members. The computer used for data storage is password protected. Any results retrieved for interim analysis and monitoring purposes will be password protected and restricted to authorized study team members. Collected data will be backed up on monthly basis and securely stored for a period not exceeding 7 years.

### Dissemination plan

The research team will simplify the study findings and disseminate to the community through local media outlets. Presentations will be made at the Ministry of Health through national Technical Working Group meetings to inform policy-makers. We will publish in international scientific peer-reviewed journals and present at international conferences.

## Discussion

The present research study intends to explore the topics of interest in a coherent and systematic way. The long-term goal of this study is to provide evidence-based information that will contribute to the development of strategies to increase women’s access to safe PAC in low-income contexts where diagnosis and services are constrained. This evidence will provide information to policy-makers in Uganda about women’s reproductive health needs related to availability and improvements in PAC, as well as counseling and contraception for all women. By evaluating the safety and effectiveness of midwives administering misoprostol for treatment of second-trimester incomplete abortion, whose management is currently restricted to physicians, the study is attempting to contribute to the reduction of maternal morbidity and mortality and to mitigate human resource problems in emergency obstetric and gynecological care. A direct economic impact can also be expected due to reduced treatment costs of complications from incomplete abortions.

## Limitations

The study is implemented at study sites with variable client caseloads due to the differing levels of health care provision. We have addressed this using blocked randomization to cater for the uneven number of participants from each site. The health care providers to whom women are randomized work closely at the clinic and within the same environment, which might affect the outcome. Health care providers’ years of working experience might differ between the two groups of midwives and doctors and by individual. Most commonly, midwives working in rural area have longer work experience than doctors. In addition, the health provider’s individual attitude and experiences of using misoprostol might further impact the outcome. All health providers at the participating health facilities will undergo standardized training to strengthen the internal validity.

## Trial status

Protocol version number: PACII 01, issued 17 November 2017. Participant recruitment began on 14 August 2018, and the approximate date recruitment will be completed is 15 August 2020.

## Data Availability

Data collection training materials are available on request. Once the study is completed, the authors plan to make the data available for wider use.

## Abbreviations

CRF: Case record form
DSMB: Data Safety Monitoring Board
ITT: Intention to treat
LMP: Last menstrual period
MOH: Ministry of Health
PAC: Post-abortion care
SAE: Serious adverse event
UNCST: Uganda National Council for Science and Technology
WHO: World Health Organization
